## Abstract

**Background:**

Clinical research is essential for medical advancement but contributes to carbon emissions through activities such as travel, data management, and laboratory processes. As healthcare systems move towards net-zero targets, there is a growing need to understand public awareness of and attitudes towards environmental sustainability in clinical research. Public and patient involvement (PPI) can enhance the relevance and acceptability of research, however there is limited evidence on how best to co-develop tools to assess public understanding of sustainable clinical research.

**Methods:**

This study is a two-phase protocol. Phase I involves the co-development of an anonymous online survey with PPI partners through two structured workshops. Survey themes, topics, questions and format will be agreed collaboratively, and the co-development process will be evaluated using qualitative data collected during the workshops. These data will be analysed thematically, using Braun & Clarke’s (2006) framework. Phase II involves distribution of the survey to clinical research, patient and public networks using an online platform. Survey data will be analysed using descriptive statistics for quantitative data and inductive content analysis for qualitative responses.

**Discussion:**

This study will generate a co-developed survey instrument and provide insights into public understanding of sustainable clinical research. Reporting on both the survey findings and the PPI co-development process will inform future research and support the development of sustainable research clinical practices.

## Introduction

Clinical research is essential for facilitating medical progress, through the development of new medicines, the generation of medical knowledge and improvements in healthcare systems and patient outcomes [1]. It provides critical evidence regarding the safety and efficacy of treatments and interventions, contributing to improved standards of care [2]. However, clinical research and healthcare activities can generate substantial carbon emissions, through a range of operational and research related activities.

Systematic reviews have estimated that global healthcare systems contribute approximately 4–5% of total greenhouse gas emissions [3]. A similar review, estimated emissions from healthcare systems accounted for between 1.5% − 9.8%, with a mean ratio of 4.9% [4]. Clinical research studies, like clinical trials, can generate significant emissions, for example the CASPS trial and PRIMETIME trials, produced and estimated 72 tonnes of CO_2_e (carbon dioxide equivalent) and 89 tonnes of CO_2_e, respectively [5]. Emissions associated with clinical research arise from activities such as sample collection and storage, data management, participant and staff travel, and the use and disposal of laboratory materials [6].

The increasing contribution of greenhouse gas emissions to climate change presents a serious global challenge, with well documented impacts on environmental stability and extreme weather events [7]. Identifying and mitigating contributors to emissions across sectors including healthcare and research is therefore an urgent priority, including strategies to reduce them.

As healthcare systems globally commit to net-zero targets [8,9], understanding public awareness of sustainable research practices is increasingly important, as a key driver to implementing positive change in reducing healthcare - and research - related emissions. This increased understanding could influence education initiatives informing patients and the public about research design changes to improve sustainable research practices. Similarly, public agreement for more sustainable research practices could influence funding bodies and policymakers to implement standard reporting and/or cost adjustments to enable more environmentally friendly research. Finally, the adoption of emission reduction strategies and promotion of studies as ‘lower carbon’ could positively influence recruitment and participation. Key stakeholders, including patients and the public, are fundamental to the development of these practices. As such, this study will include public and patient involvement (PPI) partners, to support the co-development of a survey tool exploring public understanding of sustainable clinical research.

### Aim and objectives

The aim of this study is to co-design and co-develop a survey to investigate public understanding of sustainable clinical research. The objectives are to:

Recruit PPI partners and co-develop survey themes, questions and formatDistribute the co-developed online survey to members of the publicEvaluate and report the PPI co-development processAnalyse and report the survey responses

## Methods

This study comprises two phases outlined below and summarised in Fig 1.

**Fig 1 pone.0342279.g001:**
[figure not shown]
Phase I and Phase II development processes.

### Phase I – Co-development of online survey

The survey will be co-developed through a structured process with PPI partners and is detailed below.

### Co-development process

The co-development process will involve two workshops with PPI partners. Proposed survey themes/topics will be provided in advance to support discussion (see Table 1).

**Table 1 pone.0342279.t001:** Proposed themes for discussion during workshop exercises.

	Theme	Topics
1	Awareness and Understanding of Clinical Research	Knowledge of what clinical research is and how it works Perception of the importance and benefits of clinical research
2	Willingness to Participate in Clinical Research	Factors that influence accessibility/decision-making (e.g., research location, use of digital tools, travel)
3	Instrument to assess environmental concern	Adapted environmental concern scale (to be agreed between researcher and PPI partners)
4	Environmental Concerns in Research	Views on reducing waste, energy use, travel emissions, and resource consumption in research Level of concern about environmental impact from healthcare and research
5	Understanding of the environmental impact of clinical research	Awareness of environmental and social impact of clinical research Perceptions of what makes research “environmentally friendly“
6	Equity and Access	Views on whether practices (e.g., remote participation) help or hinder inclusivity

During Workshop One, the survey topic and proposed themes, and initial generation of open – and closed – ended survey questions will be developed. Feedback from Workshop One in the form of transcripts from audio-recordings and written notes will be analysed and inform the drafting of survey questions and formatting for Workshop Two.

Workshop Two will focus on reviewing and finalising survey questions, content and gathering evaluative feedback on the co-development process. The researcher will then analyse transcripts and written notes from Worksop Two to draft the final survey and share with PPI partners for final feedback and approval. The final survey is anticipated to include five or six themes, with five questions per theme (25–30 questions). Approximate completion time is 30 minutes. However, based on question design, this may vary. PPI partners will then contribute to user testing before survey distribution.

As well as the feedback from the workshop discussions being used to inform the survey design, the evaluation feedback will be analysed to report on the co-development process.

### Consensus process

A structured consensus approach will be used, drawing on a simplified ‘card sorting’ method. This method was traditionally deployed as a method to structure the navigation of web pages but has been adapted to priority-setting in healthcare research [10]. PPI partners will propose questions, which will be discussed, grouped into themes and prioritised collaboratively during the workshops. Multiple rounds of ‘card sorting’ may be used throughout the development process to finalise questions and design.

### Recruitment of PPI partners

PPI partners will be recruited through the University College Dublin Clinical Research Centre (UCD CRC) social media channels, the UCD PPI Ignite Network and if required, the National PPI Ignite Office. Experience in clinical research or sustainability will be desirable but not a requirement.

All PPI partners will be provided with an information leaflet and consent form for participation in the co-development research exercise (see S1 File PPI partner information leaflet and consent form).

### Sample size calculation

We will aim to recruit 8–10 PPI partners to support effective discussion and representation during the co-development process.

### Data extraction

Workshop transcripts will be imported into NVivo for analysis [11]. Two researchers will independently code a subset of the data to establish consistency and reduce analytical bias. Data will be analysed thematically in NVivo [11], using Braun & Clarke’s (2006) thematic analysis framework [12]. This framework incorporates a six-step procedure for analysis of qualitative data:

step one involves data familiarisation,step two involves generation of initial codes,step three involves generation of initial themes,step four involves reviewing themes,step five involves defining and finalising themes,step six involves generation of a report.

### Data analysis

Analysis of the co-development data may be subject to researcher bias. As such, measures will be taken to reduce bias and ensure inter-rater reliability. This includes the first researcher (DK) and a second researcher independently analysing a section of data as a pilot exercise, to identify discrepancies or issues in the analysis and coding process. A feedback loop and continuous monitoring will then be employed to address iteratively any deviations in coding [13]. The first researcher will code the remaining data. The researchers will then engage in peer debriefing, where they will meet to discuss the remaining data and associated codes to identify any substantial discrepancies [13,14]. This method will be applied across both workshops. As such, Workshop One data will inform the development of survey questions for discussion at Workshop Two. Workshop Two data will inform finalisation of questions and formatting, resulting in a final survey reviewed by PPI partners.

### User testing

PPI partners and peer colleagues will contribute to user testing of the survey prior to distribution. In particular, survey accessibility, access and navigation will be key considerations to ensure there is a high degree of usability.

### Phase II – Survey methodology and distribution

The online survey will be used to:

Assess public knowledge and understanding of clinical research including awareness of environmentally sustainable research practicesExplore public attitudes and beliefs regarding sustainability in clinical researchIdentify information needs related to sustainable research practices

The survey will be anonymous and hosted on Qualitrics as a secure, UCD approved, survey platform. Participants will be informed that survey responses will be anonymised and that no personally identifiable information (PII), including IP addresses and contact information will be collected. All data will be stored on UCD servers in accordance with institutional data governance policies. This will be enabled and communicated to participants.

### Survey participant population

Survey participants will comprise members of the public with links to clinical research networks, clinical research facilities, patient/charity or advocacy organisations associated to clinical research.

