### Recruitment

Research participants will be recruited through multiple channels, including:

clinical research facilities (CRFs)clinical trial networks (CTNs)clinical research centres (CRCs)public and patient involvement (PPI) networksnational organisations, such as the Health Research Board – Trials Methodology Research Network (HRB-TMRN), Cancer Trials Ireland, and associate groups.

Colleagues within the above-mentioned networks will disseminate the survey link to potential participants. Direct contact between the researcher and survey with participants will not occur. A snowball sampling approach will be employed, whereby participants will be encouraged to share the survey link within their network [15].

In addition, the survey will be promoted via social media platforms and at public engagement events. A QR code and brief study description will be provided to enable access to the survey. To prevent duplicate responses or repeated participation, a feature in the survey software will be enabled that prevents multiple submissions.

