## Discussion

While research has been conducted in recent years to understand the environmental impact of clinical research activities, there is limited data and evidence of public knowledge and perceptions of sustainable research practices that could address this impact. Online survey research offers an increasingly common method for data collection of public perspectives, due to advances in survey software, data security, and online accessibility [20]. They facilitate efficient survey design, data collection and analysis and may achieve favourable response rates compared with traditional survey methods particularly with larger samples sizes [21].

Development of this online survey will be strengthened by the inclusion of PPI, an established research approach, that will ensure rigour in survey instrument co-development, through co-design and user testing. Evidence suggests that PPI can enhance research relevance, quality and impact by incorporating lived experience and public perspectives [22,23]. Additionally, it will ensure that survey content, language and formats are accessible, meaningful and reflective of public priorities, rather than only academic or institutional perspectives.

While the online survey approach can introduce various biases and associated limitations, the study design will mitigate for these, specifically addressing sampling, response, and order effects concerns, through co-design, diverse distribution methods, and implementation of software features to improve readability and functioning.

The findings from this study will inform of public understanding of sustainable clinical research and inform the method and output from a PPI co-development process. Limited public awareness may indicate a need for improved communication and education, whereas strong public concern could support prioritisation of investment in more sustainable research methodologies and infrastructure. The resulting findings may also inform institutional policies, funding decisions, ethical guidelines, and sustainability strategies within research organisations. Additional policy implications centred on research funders could influence adoption of routine environmental impact assessments and/or carbon budgeting for studies. Finally, the findings will further inform future research activities for a larger study looking at the development of sustainable research practices.

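### The aim and conclusions are worded for the public, but the plan defines and mainly recruits people linked to clinical research, opens eligibility to everyone, and never names that link as a limit

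*Protocol article*

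**What the plan says.** All references are to the protocol article.

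- **Who is surveyed.** Survey participant population: "Survey participants will comprise members of the public with links to clinical research networks, clinical research facilities", continuing to patient, charity and advocacy organisations associated with clinical research.
- **How they are reached.** Recruitment lists research facilities, trial networks, research centres, PPI networks and national trial organisations. "Colleagues within the above-mentioned networks will disseminate the survey link to potential participants", and "participants will be encouraged to share the survey link within their network". Social media and events for the public are added, with no indication of what share of respondents they should supply.
- **Who is eligible.** Inclusion and exclusion criteria admit adults with internet access and exclude non-English speakers. No research link is required.
- **What the study is about.** Aim and objectives: "The aim of this study is to co-design and co-develop a survey to investigate public understanding of sustainable clinical research". The Phase II purposes are likewise worded for the public.
- **What will be concluded.** Discussion: "Limited public awareness may indicate a need for improved communication and education", and "strong public concern could support prioritisation of investment in more sustainable research methodologies and infrastructure".
- **What is conceded.** Sample size says that, with non-probability sampling, estimates at population level are not intended, while still promising a sound picture of what the public thinks. Strategies to minimise bias accepts that snowballing may reduce representativeness, then says that diverse networks and channels can deal with this. It also says that snowballing makes the sampling more random.

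**The concern.** The article gives two populations that do not agree: people with a research link, and any eligible adult. The main recruitment route follows the first; the aim and Discussion are worded for neither, but for the public at large.

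This matters because the link is related to what is measured. Proposed Theme 1 in Table 1 covers "Knowledge of what clinical research is and how it works". People who belong to a trial network, a PPI group or a research-associated charity have plausibly met clinical research already, so they are likely to know more about it than others. The same may hold, less certainly, for awareness of sustainable research.

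The Discussion would read low awareness as a need for education. A mainly research-linked sample could hide that need. Unlinked respondents who arrive through social media, events or snowballing would be mixed in, in an unknown proportion. As responses are anonymous and no contact details are kept, a respondent's link cannot be recovered later if the survey does not ask about it.

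**Working it through.** **1. The plan's own figure.** Inputs from Sample size: margin e = 5%, confidence 95% (z = 1.96), response distribution p = 50%.

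- Infinite population: n = z²p(1−p)/e² = 0.9604/0.0025 = 384.1, so 385.
- Finite population of N: n = Nx/((N−1)e² + x), with x = z²p(1−p) = 0.9604. At N = 20,000 this gives 376.9, so 377.

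The stated 377 is therefore reproduced exactly at N = 20,000, a size that the article does not state, and lies within 3% of the infinite-population figure. At n = 377 the margin is 1.96 × √(0.25/377) = 5.05 points. This margin covers random error only and says nothing about who was sampled.

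**2. The size of a selection effect.** The article gives no awareness rates and no linked share, so every input here is an assumption. Let f be the linked share of the sample, s the linked share of the public, and pL and pU the proportions aware among linked and unlinked people.

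- Sample value: f·pL + (1−f)·pU
- Public value: s·pL + (1−s)·pU
- Excess: (f − s)(pL − pU)

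With s = 5% and pL = 60%, the excess in percentage points is:

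| Linked share of sample | pU = 50% | pU = 40% | pU = 30% |
|---|---|---|---|
| 100% | 9.5 | 19.0 | 28.5 |
| 80% | 7.5 | 15.0 | 22.5 |
| 50% | 4.5 | 9.0 | 13.5 |

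Example: (0.50 − 0.05) × (0.60 − 0.50) = 4.5 points. With s = 10% the values are slightly smaller: 9, 18 and 27 points at f = 100%, and 4, 8 and 12 points at f = 50%.

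A nominal 95% interval at n = 377 would cover the public value about 58% of the time in the mildest cell of the table (4.5 points), and at most about 4% of the time when the whole sample is linked. More respondents would narrow the interval but would not move its centre.

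**3. Precision after splitting by link.** If 30% of respondents are unlinked (assumed), 0.30 × 377 is about 113. Their margin is 1.96 × √(0.25/113) = 9.2 points. The other 264 have 1.96 × √(0.25/264) = 6.0 points. As with the 5-point figure, these margins are nominal, because the sample is not random.

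**The case against.** The strongest reply is that the restriction rests on one sentence. The eligibility criteria require no link, social media and events extend the reach, and the Abstract speaks of public as well as research and patient networks. This stands to the extent that the sample will not be purely research-linked. It does not settle the matter, because it leaves two conflicting population definitions, and the named recruitment channels still follow the narrower one.

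A second reply is that the limits are acknowledged. That is partly so. However, the Sample size caveat concerns non-probability sampling in general, and the bias section presents the loss of representativeness as something that the chosen networks can address. Neither says that respondents will mostly be connected to research, and the Discussion carries neither caveat.

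A third reply concerns direction and consequence, and much of it stands. The Discussion's awareness conclusion follows text on sustainable research practices, not on general knowledge of research, and nothing in the article shows that a research link raises the former. The Discussion is worded tentatively and sets no threshold. If even linked respondents show low awareness, the case for education becomes stronger; the risk is confined to awareness looking high.

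A reader might also infer that willingness to take part will be overstated, since "Willingness to Participate in Clinical Research" is a proposed theme. The article does not support making that part of the point: the only topic listed under that theme is the factors behind access and decisions, the themes are still proposals, and the Discussion draws no conclusion on willingness.

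Finally, the survey has yet to be co-developed, so the absence of a question on research link is not itself an error.

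**Conclusion.** The mismatch is in the text and stands: the defined population and main channels are research-linked, eligibility is open, the aim and conclusions are for the public, and no section names the link as a limit. Knowledge of clinical research is likely to look higher than in the general public, and awareness of sustainable research possibly so. No direction is claimed for environmental concern.

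The size is unknown. On the assumed inputs with s = 5% it runs from about 4.5 points, just inside the margin of about 5, to 28.5 points, far outside it.

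A reader might go further and infer that awareness will certainly be overstated, by a large and known amount. For instance, assuming 70% awareness in linked people, 40% in unlinked people, 10% of the public linked and a sample 70% to 100% linked gives (0.70 − 0.10) × 30 = 18 to (1.00 − 0.10) × 30 = 27 points. The documents support neither the certainty nor that range: none of these inputs comes from the article, and a smaller gap or a more mixed sample gives an excess close to or within the margin.

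**What to change.** The study is still recruiting PPI partners, so all of this can be done before the survey is written.

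1. Reconcile Survey participant population with Inclusion and exclusion criteria, so that one population is defined.
2. Put to the PPI partners one closed question on the respondent's link to clinical research, with broad, non-identifying categories such as trial participant, patient or advocacy group member, PPI contributor, and none.
3. Report the main awareness and concern items by link status as well as overall.
4. Word the aim and the Discussion's conclusions for the people actually reached, who will mainly be research-connected, and repeat the Sample size caveat in the Discussion.
5. Remove the statement in Strategies to minimise bias that snowballing makes sampling more random. It recruits through existing contacts and does not do that.

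The cost is one extra question, one cross-tabulation, a narrower conclusion and less precision within groups: about ±9 points for the unlinked if they number roughly 113 of 377, and about ±6 points for the rest.
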